#### Cost-effectiveness

The hypothesis is that the new model will be dominant (that is, lower total costs with an increased prevalence of treatment) or highly cost-effective (that is, marginally increased total costs with a significant decrease in the prevalence of untreated caries). We construct an incremental cost-effectiveness ratio with incremental total costs of the PREDICT minus those of the control divided by the difference in the proportion of patients who have untreated caries in PREDICT minus the proportion of patients with untreated caries in the control. We use bootstrapping to estimate a 95 % confidence range for the cost-effectiveness ratio.

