**Methods/Design:**

This is a parallel-group cluster randomized controlled trial. Fourteen rural Oregon counties with a publicly insured (Medicaid) population of 82,000 children (0 to 21 years old) and pregnant women served by a managed dental care organization are randomized into test and control counties. In the test intervention (PREDICT), allied dental personnel provide screening and preventive services in community settings and case managers serve as patient navigators to arrange referrals of children who need dentist services. The delivery system intervention is paired with a compensation system for high performance (pay-for-performance) with efficient performance monitoring. PREDICT focuses on the following: 1) identifying eligible children and gaining caregiver consent for services in community settings (for example, schools); 2) providing risk-based preventive and caries stabilization services efficiently at these settings; 3) providing curative care in dental clinics; and 4) incentivizing local delivery teams to meet performance benchmarks. In the control intervention, care is delivered in dental offices without performance incentives. The primary outcome is the prevalence of untreated dental caries. Other outcomes are related to process, structure and cost. Data are collected through patient and staff surveys, clinical examinations, and the review of health and administrative records.

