### Study measures and data collection

The primary and secondary study measures for impact and process outcomes are presented in Table 1.

**Table 1 Tab1:** PREDICT study measures: impact and process outcomes

Type of outcome	Outcome measures	Description	Operationalization
Impact: primary	Oral health	Proportion of children with untreated dental caries	Number of Medicaid ADS-assigned children with untreated caries divided by the number of children enrolled in Medicaid and assigned to ADS.
Impact: secondary	Patient/consumer satisfaction	Mean quality of care	Mean score for the ratings of quality of care from the parent survey
Process: primary	Dental care utilization by children	Percentage of children who received a dental service	Number of Medicaid-enrolled ADS-assigned children who received a dental service (any CDT code) divided by the number of Medicaid-enrolled ADS-assigned.
Process: primary	Consent for treatment at community settings	Proportion of children for whom consent is obtained	Number of Medicaid ADS-assigned children for whom consent is obtained divided by the number of Medicaid ADS-assigned children.
Process: primary	Oral health screening and risk assessment	Proportion of children who received screening and risk assessment	Number of Medicaid-enrolled ADS-assigned children who received both a screening (CDT 0191) and a risk assessment (CDT 0601-D0603) divided by the number of Medicaid-enrolled ADS-assigned children.
Process: primary	Timely need-based curative treatments	Proportion of children referred for dentist treatment who receive care within 60 days of screening	Number of Medicaid-enrolled ADS-assigned children with dentist treatment needs who visited the dentist (CDT D1000 to D9999) within 60 days of screening divided by the number of Medicaid-enrolled ADS-assigned children with dentist treatment needs.
Process: primary	Dental care utilization by pregnant women and new mothers	Percentage of pregnant women and new mothers who received a dental service	Number of Medicaid-enrolled ADS-assigned pregnant women who received a dental service (any CDT code) divided by the number of Medicaid-enrolled ADS-assigned pregnant women and new mothers.

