### Statistical analysis

#### Sample size

Based on seven test counties and seven control counties, the power is at least 80 % to detect an increase in dental care utilization from pre- to post-implementation within the test counties or an increase in utilization between test and control counties post-implementation of approximately 10 percentage points for utilization rates of 5 % to 10 %, 15 percentage points for utilization rates of 20 % to 30 %, and 20 percentage points for utilization rates of 40 % to 50 %. Estimates are conservative, based on an intracounty correlation (ICC) of 0.05. Pilot data on dental care utilization indicated ICCs were less than 0.05 for cluster sizes of 200 or more children, and ICCs were less than 0.02 for cluster sizes greater than 500 children. Using a sample size of 80 children per county pre- and post-implementation and an ICC of 0.05, we estimate power is 80 % to demonstrate a 15 percentage point or larger decrease in prevalence of untreated dental caries, assuming a prevalence of untreated caries of 25 % in the control counties. In 2012, 25 % of 6 to 10 years old from low-income families in Oregon had untreated dental decay [28]. Using a sample size of 20 parents per county pre- and post-implementation we estimate power is 84 %, based on a two-sided 0.05 significance level, to detect a medium effect of the intervention on dental care ratings (for example, an average increase of 0.75 points) (CAHPS; range 1 to 10), assuming SD = 1.5 in patient satisfaction scores [29].

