Both the evaluation and effective management of this intervention depend on the availability of operational data. First, staff members have to complete annual environmental scans of test and control counties. These scans address differences among counties in availability of dentists, community prevention programs, population income and ethnicity, etc. Second, data are needed on community settings and schools for planning the intervention and evaluation. Third, data are needed on the characteristics and oral health of the children who do/do not consent for the program. Finally, the costs and services provided in test and control dental delivery systems need to be assessed. Determining the categories of cost that are incremental to evaluation versus care delivery (for example, analysis costs and any space, time, and supply costs unique to the evaluation) will also be important. This requires a clear understanding and measurement of all costs, so costs specific to the evaluation can be identified. Realistically, the final cost assignment is best done retrospectively. This is because some evaluation costs may cover business or clinical processes that turn out to be critical for the effective management of the program. As such, they should be considered care delivery costs.

The key to this intervention is effective management and HIT support. Managers and staff members need monthly management reports so they can adjust to problems that arise. ADS has substantial public relations and financial risk, so it is incentivized to make an all-out implementation effort. This “real’ world” operational environment increases the chances for success and the generalizability of the results. Indeed, if the intervention is cost-effective, ADS plans to make it the primary delivery model for Medicaid children and mothers.

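### The cost-effectiveness hypothesis defines dominance by more treatment, while its other branch and the ratio use untreated caries, the primary outcome

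*Protocol article*

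**What the plan says.** The Cost-effectiveness section of the protocol article states a hypothesis with two branches.

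- **Dominant:** the new model is "dominant (that is, lower total costs with an increased prevalence of treatment").
- **Highly cost-effective:** "marginally increased total costs with a significant decrease in the prevalence of untreated caries".

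The section then defines the incremental cost-effectiveness ratio. Its numerator is the difference in total costs, PREDICT minus control. Its denominator reads: "the difference in the proportion of patients who have untreated caries in PREDICT minus the proportion of patients with untreated caries in the control". A bootstrap 95 % range is planned for the ratio.

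Elsewhere the article separates oral health from service use. The abstract says: "The primary outcome is the prevalence of untreated dental caries". Table 1 lists "Proportion of children with untreated dental caries" as the primary impact outcome and "Percentage of children who received a dental service" as a process outcome. Table 1 also has process measures for timely curative care and risk-based preventive care. No section defines prevalence of treatment or says how it relates to untreated caries.

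**The concern.** Dominance and the ratio should describe the same cost-and-effect plane. Here one sentence uses two effects, and the stronger label is the one that leaves out the primary outcome.

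The two effects can separate in this trial. PREDICT delivers services in community settings and pays teams for meeting performance benchmarks, so a treatment measure can rise because the programme is running, whether or not disease falls. The reverse is also possible. The Discussion expects the share of patients needing a dentist's curative care to shrink over time as existing disease is dealt with and new disease is prevented, so successful prevention could come with less curative treatment.

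At stake is what the economic analysis may conclude. The section on cost per member per month hypothesises lower total costs, so dominance is a branch the investigators expect to reach. As worded, it could be claimed without an oral-health gain, or withheld despite one.

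**Working it through.** The section gives no ratio, threshold or power figure, so there is no stated number to reproduce. The check compares two definitions of dominance.

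**Definitions**

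- By the wording: cost difference < 0 and treatment difference > 0.
- On the ratio's effect: cost difference < 0 and untreated-caries difference < 0.
- Ratio = cost difference / (untreated caries in PREDICT - untreated caries in control).

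**Inputs**

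- Untreated caries in control, 25 %: from Sample size, "assuming a prevalence of untreated caries of 25 % in the control counties".
- Everything else is assumed for illustration: a cost difference of 2 per member per month in either direction, treatment 55 % or 45 % in PREDICT against 45 % in control, and untreated caries of 20 % to 30 % in PREDICT.

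| Case | Cost difference | Treatment difference | Untreated caries, PREDICT vs control | Ratio | Dominant by the wording | Dominant on the ratio's effect |
|---|---|---|---|---|---|---|
| a | -2 | +10 points | 25 % vs 25 % | -2 / 0, undefined | yes | no |
| b | -2 | +10 points | 27 % vs 25 % | -2 / 0.02 = -100 | yes | no |
| c | -2 | +10 points | 20 % vs 25 % | -2 / -0.05 = +40 | yes | yes |
| d | -2 | 0 | 20 % vs 25 % | -2 / -0.05 = +40 | no | yes |
| e | +2 | 0 | 30 % vs 25 % | 2 / 0.05 = +40 | no | no |
| f | +2 | +10 points | 20 % vs 25 % | 2 / -0.05 = -40 | no | no |

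**Reading the table**

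1. In cases a and b the wording grants dominance with no gain, or a loss, in oral health.
2. In case d the wording withholds dominance although PREDICT is cheaper and has less untreated caries.
3. In case c the two definitions agree.
4. Cases c and e give the same ratio, +40, although one is cheaper and better and the other dearer and worse. With this denominator a benefit is negative, so the sign of the ratio does not identify dominance and cannot stand in for a clear verbal definition.

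**Could treatment be the mirror image of untreated caries?** Suppose every child with caries experience is either untreated (share U) or fully treated (share T), so that U + T = E, the share with caries experience. Then the change in U equals the change in E minus the change in T. More treatment means an equal fall in untreated caries only if E does not differ between the arms. A child with both treated and untreated teeth breaks the identity, and a measure that counts preventive or any dental services is not bound by it at all.

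**The case against.** The strongest reply is that this is loose wording in a hypothesis. The section gives no instruction to classify a result as dominant when treatment rises, and treatment enters no calculation. The operative method is the ratio, which uses the right outcome. In that setting a higher prevalence of treatment may simply mean fewer children left untreated. A rise in untreated caries would also be visible in the primary analysis and in the ratio's denominator.

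Much of this stands. The ratio is unaffected, no estimate or test changes, and the figures in the table are illustrations with no claim to likelihood. On a purely curative reading, case a would need caries experience to be 10 points higher in PREDICT. But the article does not state that reading, and its wording is introduced as the meaning of the term, so it is not a detail left to a fuller plan.

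Two stronger readings are tempting and are not supported.

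- A reader might infer that adoption would rest on the treatment measure, because the Discussion says that "if the intervention is cost-effective, ADS plans to make it the primary delivery model for Medicaid children and mothers". That remark speaks of cost-effective, not dominant, and both the highly cost-effective branch and the ratio rest on untreated caries. It is also a statement of the organization's intentions, not an analysis criterion.
- A reader might infer that treatment has no counterpart among the trial's outcomes. The exact term is absent from Table 1, but receipt of a dental service, timely curative care and risk-based preventive care are all listed there as process outcomes.

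**Conclusion.** The inconsistency is real and lies within the Cost-effectiveness section. The dominance branch is stated on a treatment measure; the other branch and the ratio are stated on the primary outcome. The two definitions disagree in two situations: costs fall and treatment rises but untreated caries does not fall (cases a and b), and costs fall and untreated caries falls but treatment does not rise (case d).

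The effect is confined to when the dominance hypothesis may be called met. The conclusion assumes only that the phrase means what it says and that treatment and untreated caries can move separately, as Table 1's split into process and impact outcomes allows. How often the definitions would disagree in practice cannot be judged from the article. If the phrase was a slip, correcting it loses nothing; if it was intended, it permits a dominance claim without a gain in oral health.

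**What to change.** Define dominance on the ratio's own effect: lower total costs with a lower prevalence of untreated caries than control. Judge it from the signs of the cost and caries differences, not from the sign of the ratio. Report treatment measures only as process outcomes, with no part in the dominance or cost-effectiveness conclusion.

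Under this definition cases a and b are no longer dominant, c stays dominant, and d becomes dominant.

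The cost is one changed phrase and a sentence on reporting. No new data are needed, since both differences are already required for the ratio. The downside is that the dominant label may be harder to earn.

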#### Economic outcomes

Economic outcomes include the costs for the following:Outreach activities: actual FTE expenditures on community outreach.Oral health screening and caries risk assessment.Preventive treatment.Restorative treatment.Dental care.Total dental: sum of outreach and dental care costs.Outpatient medical.Emergency department visits.Inpatient hospitalizations. Total medical. Outpatient prescriptions. Total cost: Sum of dental, medical, and prescription costs.

Potential confounders or effect modifiers at the county level include the percentage of participants in different age categories, at elevated caries risk, and in different race/ethnicity categories.

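### The cost-effectiveness ratio subtracts untreated caries in the direction that makes its denominator negative when PREDICT works, and the dominance definition uses a different effect

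*Protocol article*

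**What the plan says.** In the protocol article, the Cost-effectiveness section sets out three things.

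- **The ratio.** The numerator is "incremental total costs of the PREDICT minus those of the control". The denominator is "the difference in the proportion of patients who have untreated caries in PREDICT minus the proportion of patients with untreated caries in the control".
- **The hypothesis.** PREDICT will be either dominant, explained as "lower total costs with an increased prevalence of treatment", or highly cost-effective, explained as "marginally increased total costs with a significant decrease in the prevalence of untreated caries".
- **The uncertainty.** "We use bootstrapping to estimate a 95 % confidence range for the cost-effectiveness ratio".

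The section takes no absolute value, does not speak of cases averted, and gives no rule for saying which quadrant of the cost and effect plane a ratio belongs to. The Discussion adds that the dental care organization intends to make PREDICT its main model for Medicaid children and mothers if it proves cost-effective.

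**The concern.** Cost and effect are both taken as PREDICT minus control, but the effect is a harm that the trial expects to fall. Under both parts of the hypothesis the denominator is therefore negative. A reader used to a cost per unit of benefit will take a positive ratio as a price and a negative one as a saving with benefit. Under the stated formula each means the opposite.

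Two further features of the section add to this. Dominance is worded on one effect and the ratio is built on another, so a result could be called dominant on a measure that the ratio does not contain. The only stated measure of uncertainty is a range for the ratio itself, and such a range loses its meaning when either difference may change sign.

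What is at stake is the reading of the result on which adoption is said to depend. The estimates of cost and of caries are not affected.

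**Working it through.** The article gives no cost figure, ratio or willingness-to-pay value, so there is no stated ratio to reproduce. The check is algebra on the formula, followed by the precision implied by the Sample size section.

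**1. Sign of the ratio.** Inputs: untreated caries of 25% in control and a 15-point reduction, hence 10% in PREDICT (Sample size section). The cost difference is assumed to be 100 units either way, and only its sign matters. In the two worse rows the prevalences are swapped.

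- As written: (cost PREDICT - cost control) / (p PREDICT - p control)
- Reversed: (cost PREDICT - cost control) / (p control - p PREDICT)

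| PREDICT is | Cost difference | Denominator as written | Ratio as written | Ratio reversed |
|---|---|---|---|---|
| cheaper, better (dominant) | -100 | -0.15 | +667 | -667 |
| costlier, better | +100 | -0.15 | -667 | +667 |
| costlier, worse (dominated) | +100 | +0.15 | +667 | -667 |
| cheaper, worse | -100 | +0.15 | -667 | +667 |

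Reversing the denominator restores the usual reading of the second row: 667 units paid per case of untreated caries averted. It does not separate the first row from the third, or the second from the fourth. No ratio can do that on its own.

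**2. The two effects side by side.** Dominance is tied to more treatment. The highly cost-effective case and the ratio are tied to less untreated caries. Table 1 makes untreated caries the primary impact outcome, while its measures of treatment received are process outcomes. Treatment can rise without untreated caries falling, so the two wordings are not interchangeable.

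**3. Can the denominator change sign in the bootstrap?** Inputs from the Sample size section: 7 counties per arm, 80 children per county, ICC 0.05, 25% in control.

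Check on the inputs: the design effect is 1 + 79 x 0.05 = 4.95, and 560 / 4.95 = 113.1 effective children per arm. For 25% against 10% this gives power of 79.4% with a t reference on 12 degrees of freedom (84.8% with a normal reference). The stated 80% is reproduced.

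Standard error of the post-implementation difference: SE = sqrt([p1(1 - p1) + p2(1 - p2)] x (0.05 + 0.95/80) / 7). The probability that the estimate has the wrong sign is the normal tail beyond (true reduction)/SE.

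| True reduction | SE | Reduction/SE | Probability of wrong sign |
|---|---|---|---|
| 25% to 20% | sqrt(0.3475 x 0.061875 / 7) = 0.0554 | 0.90 | 18.3% |
| 25% to 15% | sqrt(0.3150 x 0.061875 / 7) = 0.0528 | 1.90 | 2.9% |
| 25% to 10% | sqrt(0.2775 x 0.061875 / 7) = 0.0495 | 3.03 | 0.1% |

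If the trial observes exactly the true reduction, about this share of bootstrap replicates has a denominator on the other side of zero. A 95% range leaves 2.5% in each tail. The problem is therefore clear at 5 points, borderline at 10 and absent at the planned 15.

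**4. Can the numerator change sign?** The plan's own hypothesis covers both lower and marginally higher total costs. The Economic statistical analysis plan expects total costs to fall, while the Discussion expects total expenses to rise as more people are treated. A cost difference near zero is thus a live possibility. Even with a stable denominator, the range would then mix dominant with costlier-but-better replicates. Within the dominant quadrant the size of the ratio has no useful order: as written, a saving of 100 with 15 points gives 667, and the same saving with only 10 points gives 100/0.10 = 1,000.

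**The case against.** The strongest reply is that this is a matter of presentation. Cost is a secondary objective. The sign convention changes neither the cost difference nor the caries difference, both of which are analysed separately, so a careful reader could place the result in its quadrant. That stands, and it limits the weight of the point. The formula is nevertheless stated, and stated in a form that prints the hoped-for result with the unexpected sign. This is not detail that a condensed article leaves to a fuller plan.

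It is also fair to say that opposite quadrants share a ratio under any sign convention. One might infer that the stated sign is what makes opposite conclusions indistinguishable. The first table shows otherwise, which is why reversing the sign is not a sufficient repair.

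On the bootstrap, the reply that the planned effect is safe is correct at 15 points. The probabilities above also refer to repeated trials and to a post-implementation comparison. The analysis plan models pre-to-post change, whose standard error depends on a within-county correlation that the article does not give. Choice of resampling unit is commonly left to an analysis plan, and the article does not say that counties will be ignored.

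Two stronger readings are tempting, and the article supports neither.

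- **That PREDICT's cost is understated because incentive payments are left out.** Economic outcomes names no incentive line; it gives "Total dental: sum of outreach and dental care costs" and then adds medical and prescription costs. But outreach is costed as actual staff expenditure, the payroll ledger is a listed data source, the Discussion calls for all costs to be measured, and control counties also have incentives, mainly for dentists. No amounts are given for either arm.
- **That the split between evaluation and care costs is tilted toward PREDICT.** The Discussion says "Realistically, the final cost assignment is best done retrospectively". It does not say that this follows sight of the results by arm. Its stated reason is that some evaluation costs may need to be counted as care delivery, which adds to care costs.

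**Conclusion.** The point holds as a definitional error with a consequence for reporting. As written, the dominant result prints as positive (+667 in the illustration) and the costlier-but-better result as negative (-667). This follows from the formula alone and needs no assumption about the size of costs. The mismatch between the dominance wording and the ratio's effect is also plain from the text.

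The difficulty with the bootstrap range is conditional. It arises if the cost difference is near zero, or if the caries effect is well below the planned 15 points (wrong-sign probability about 18% at 5 points, 3% at 10, 0.1% at 15). Those figures assume the article's ICC of 0.05, 80 children per county, a normal approximation and a post-implementation comparison.

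The primary outcome, the data to be collected and the two component estimates are untouched. On incentive payments, the most that can be asked is a statement of where they enter total cost in each arm.

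**What to change.** - Define the effect as control minus PREDICT, that is, cases of untreated caries averted. Use it as the denominator and as the only effect in the definitions of dominant and highly cost-effective.
- Report the cost difference and the effect difference, each with its interval, and name the quadrant. Quote a ratio only where that quadrant makes it meaningful.
- Report incremental net benefit over a stated range of willingness to pay w per case averted: w x (p control - p PREDICT) - (cost PREDICT - cost control). In the illustration this is 0.15w + 100 for dominant, 0.15w - 100 for costlier and better, -0.15w - 100 for dominated, and -0.15w + 100 for cheaper and worse. The dominant case is always positive and the dominated case always negative, and nothing is divided by a quantity that may be near zero.
- Bootstrap cost and effect together, resampling whole counties within arm.
- For clarity, state where incentive payments in both arms enter total cost.

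The cost is protocol wording, agreement on a willingness-to-pay range and a little more analysis. No new data are needed.

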#### Randomization and blinding

Each County is considered a single cluster. Clusters are randomized with equal probability to the test or control interventions, using computer-generated random numbers. The allocation schedule for random assignment is generated at the University of Washington by the project biostatistician. The treatment allocation for each cluster is kept in Seattle, and the biostatistician informs local investigators about the treatment allocation, when they are ready to conduct the environmental scan of the test sites. Interviewers are blinded to group allocation. Because of the type of the intervention, personnel involved in the delivery of the intervention and participants are not blinded to group allocation.

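### The only uncertainty statement for cost-effectiveness is a 95% range of a ratio, which cannot be interpreted if the untreated-caries difference is not clearly away from zero

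*Protocol article*

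**What the plan says.** The Cost-effectiveness section sets out two ways for PREDICT to succeed. In one it costs less in total and more disease is treated (dominant). In the other it costs slightly more and untreated caries falls significantly (highly cost-effective). The summary statistic is a ratio. Its numerator is "incremental total costs of the PREDICT minus those of the control". Its denominator is the "difference in the proportion of patients who have untreated caries in PREDICT minus the proportion of patients with untreated caries in the control", so a benefit is a negative denominator. The uncertainty statement is: "We use bootstrapping to estimate a 95 % confidence range for the cost-effectiveness ratio". The section names no resampling unit, no type of bootstrap interval, and no net-benefit or cost-effect-plane summary.

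Randomization and blinding says: "Each County is considered a single cluster". The Statistical analysis plan section adjusts the outcome models for correlation within county, and the cost-per-member section adjusts for variance within cluster. The Discussion states that "if the intervention is cost-effective, ADS plans to make it the primary delivery model for Medicaid children and mothers".

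**The concern.** A ratio of two signed differences does not show which signs produced it. Under the plan's convention:

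| Cost difference | Caries difference | Meaning | Sign of ratio |
|---|---|---|---|
| negative | negative | cheaper, better (dominant) | positive |
| positive | positive | dearer, worse (dominated) | positive |
| positive | negative | dearer, better | negative |
| negative | positive | cheaper, worse | negative |

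Reversing the sign of the denominator only swaps the last column. As the caries difference approaches zero, the ratio goes to plus or minus infinity. A range that orders such replicates on one line then has no meaning. The hypothesis itself lets total cost move either way, so the numerator's sign is open by design. Only a clearly nonzero denominator keeps the ratio interpretable. At stake is whether the economic result can answer the question that the organization links to adoption.

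**Working it through.** **Inputs** (Sample size section): "Based on seven test counties and seven control counties"; "Using a sample size of 80 children per county pre- and post-implementation and an ICC of 0.05"; 25% untreated caries in control counties; a 15-point decrease with 80% power. Two-sided 0.05 is stated for the parent survey and assumed here for caries.

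**1. Reproduce the plan's power.** Design effect = 1 + (80 − 1) × 0.05 = 4.95. Effective n per arm = 7 × 80 / 4.95 = 113.1. For 25% versus 10%, SE = √[(0.1875 + 0.0900) / 113.1] = 0.0495. Power is 79.4% with t on 12 df and 80.1% with a normal test counting six clusters per arm. A plain pooled normal test gives 84.8%. The stated 80% is reproduced, so this SE is a fair basis for the denominator.

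**2. Share of replicates with the wrong effect sign.** If the estimated reduction is d and the replicates carry county-level variation, the share with a caries difference at or above zero is about Φ(−d/SE), where SE = √[(0.1875 + (0.25 − d)(0.75 + d)) / 113.1].

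| Estimated reduction d | SE | d/SE | Wrong-sign share |
|---|---|---|---|
| 15 points | 0.0495 | 3.03 | 0.1% |
| 10 points | 0.0528 | 1.90 | 2.9% |
| 5 points | 0.0554 | 0.90 | 18% |

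**3. What this does to the ratio.** The documents give no cost difference or cost variance. As an illustration only, assume the cost difference per member per month has SE 3, is independent of the caries difference, and has mean +2, 0 or −2. The chance that PREDICT is dearer is then Φ(2/3) = 0.748, 0.5 or 0.252. For d = 5 points, multiply these by 0.8165 (better) and 0.1835 (worse):

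| Assumed mean cost difference | Positive ratios: dominant / dominated | Negative ratios: dearer-better / cheaper-worse | 2.5 to 97.5 percentiles of ratio (simulated) |
|---|---|---|---|
| +2 | 21% / 14% | 61% / 5% | about −585 to +527 |
| 0 | 41% / 9% | 41% / 9% | about −458 to +459 |
| −2 | 61% / 5% | 21% / 14% | about −526 to +583 |

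In the first row, dominant and dominated replicates sit together among the positive ratios in a proportion of about 3 to 2, and the range does not separate them. At d = 15 points with mean +2, the dominated share is 0.0012 × 0.748 = 0.1%, so mixing is negligible.

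**4. Sensitivity to a pre-to-post contrast.** The outcome models compare changes, whereas the ratio is written as a simple difference between arms. For a change contrast, SE = √{[3 × 0.1875 + (0.25 − d)(0.75 + d)] × [0.95/560 + 0.05(1 − r)/7]}, where r is the county-level pre-post correlation (not given). For r from 0.7 down to 0, the wrong-sign share is 0.1% to 2.4% at 15 points, 2.6% to 10% at 10 points and 17% to 27% at 5 points. The pattern is the same, or worse if r is low.

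**5. County bootstrap with few clusters.** In a simulation (beta-binomial counties, ICC 0.05, seven per arm, 3,000 trials of 1,000 replicates), a nominal 95% percentile interval for the caries difference from resampling whole counties covered 89% to 91%.

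**The case against.** **The interval type is not stated.** The plan does not say percentile, so naive ordering of replicates is not fixed. That is true, but the quadrant problem belongs to the ratio scale. No bounded interval on that scale separates the quadrants when the denominator may be zero.

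**The components are analysed separately.** Readers will have the signed caries and cost differences from their own clustered models and need not infer the quadrant from the ratio. This stands in part: the point estimates will show the quadrant. Their separate intervals do not give the joint uncertainty, which is what the hypothesis concerns and what the bootstrap was meant to supply.

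**The problem may be rare.** A reader might note that the chance of the 95% caries interval including zero is 14% at a true 15-point effect, 53% at 10 and 85% at 5 (normal approximation, post-period contrast), and infer that the range would mislead that often. That does not follow. Those figures are one minus power, apart from a negligible opposite tail. An interval that just includes zero has only about 2.5% of replicates beyond it. Serious mixing needs a modest estimated effect, as in the table of wrong-sign shares.

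**The resampling unit.** A reader might infer from the mention of proportions of patients that patients are resampled and counties ignored. The article does not say so. That phrase defines the denominator, the other analyses adjust for clustering, and the unit is a detail that an article may leave to a fuller plan.

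**The adoption link.** The Discussion ties adoption to cost-effectiveness in general. It does not make the bootstrap range the criterion.

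**Conclusion.** The concern holds for the choice of summary. That choice is stated in the article, so it is not a detail left to another document. A 95% range of the ratio cannot support or reject the stated hypothesis unless the caries difference is clearly away from zero. On the plan's own figures the range is usable at an estimated 15-point reduction, somewhat affected at 10 points and uninterpretable at 5. A 15-point effect means cutting prevalence from 25% to 10%, so a smaller estimate deserves provision.

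The wrong-sign shares assume a normal approximation, ICC 0.05, the post-period contrast and replicates that reflect county variation. The cost figures are illustrative, and the documents allow no interval for the ratio itself. Clustering is a request to carry the existing adjustment through and to say how; the documents show no error there. This is a secondary economic analysis, but one that bears on adoption, so the change is worth making before data are analysed.

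**What to change.** In the Cost-effectiveness section, keep the ratio as a point estimate and replace its bootstrapped range with incremental net benefit:

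NB(λ) = λ × (control proportion − PREDICT proportion with untreated caries) − (PREDICT cost − control cost).

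State in advance the range of λ, the value per untreated-caries case averted. The article gives none, so the team must choose and justify it. Report NB(λ) with its 95% interval across that range, and show the joint cost-effect plane.

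Carry the county clustering into this analysis. Costs come from all enrolled children and caries from a random sample, so county is the natural unit at which to join them. The preferred method is to compute net benefit for each county and compare arms with t on 14 − 2 = 12 df. A plain county percentile bootstrap is not enough with seven counties per arm, since it covers only about 90%. If a bootstrap is kept for the plane, name the resampling unit and keep each county's cost and caries data together.

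Cost: revised wording and a short program, with no new data. Downside: results appear over a range of values rather than as one ratio, and intervals may be wider.
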